### Facilitation of interventions and motivation of participants to adherence in trial

The implementations of the interventions are being monitored during monthly check up visits by a research nurse to the participating office units. During the visits the research nurse checks the availability of hand soap and/or alcohol disinfectant products, receives comments on weekly reporting and supports participants in continuation and commitment to the hand hygiene behavior of the unit in order to increase compliance and minimize loss-to-follow-up. Any new employees volunteering to participate in the study will also receive guidance to intensified hand hygiene and behavioral habits during the visits. The participants are receiving monthly an electronical popularized information spot concerning viral diseases as an incentive and motivation to maintain agreed hand hygiene and behavioral habits.

### Evaluation of adherence to instructions

There is no way to directly measure whether the participants of this kind of an intervention study in real life follow the given instructions. Some indirect ways were considered on top of the sporadic observational information obtained during the monthly visits of the research nurse to the cluster sites. First, we wanted to monitor the usage of soap and disinfectant cluster-wise at the work place and individually at home. However, it turned out that this was not feasible, because of complex organization of the maintenance of the toilet and washing facilities in the participating companies. So, we were left with another questionnaire, a self-reporting survey of hand hygiene behavior. A survey to study hand hygiene behavior was executed among the volunteers in the beginning of the study, in January-February 2009, before the results of the contagion risk survey were published and the intervention arms designated (Additional file 3). The survey was planned to be repeated at least in the end of the study. The results of the surveys will also be used to evaluate comparability of clusters within the triplets and of the intervention arms.

### Monitoring of concurrent virus circulation in the source population

It was decided that no attempt will be made to find out the etiology of every reported infection episode. Samples for virological analysis are being collected to monitor circulation of agents causing respiratory and gastrointestinal complaints in the participating companies. Participants of the study were not especially encouraged to deliver samples for virological analysis. Rather, samples are being retrieved from any patients with respiratory or gastrointestinal symptoms attending the occupational health clinics located in the premises of the participating companies, thus originating also from people working in company units not included in the study. The seven participating occupational health clinics were advised to collect 2-3 respiratory samples per week. Fecal samples from gastrointestinal patients were advised to be taken when an outbreak was suspected, up to five specimens per outbreak.

Nasal and pharyngeal stick samples from patients with respiratory symptoms are taken by standard techniques. They will be analyzed with validated real-time polymerase chain reaction (PCR) techniques for the following viruses: influenza viruses A and B, respiratory syncytial virus, parainfluenza viruses 1, 2, and 3, adenoviruses, human rhinoviruses and human enteroviruses. Fecal samples will be taken from patients with gastrointestinal symptoms. They will be tested for noroviruses with validated real-time reverse transcriptase (RT)-PCR technique.

### Ethical issues

Participation in the study is voluntary to office employees. At the time of recruitment all potential participants received an electronical information sheet of the study, at the end of which the willingness to participate was asked. Informed consent for virological sample analysis is being obtained from patients visiting occupational health clinics because of respiratory or gastrointestinal symptoms.

The person register formed in the study is being stored in locked facilities and in secured electronic files. Personal data collected was limited to email address and working unit. Privacy protection is ensured with use of secured internet connections for data collection. The results of virological sample analysis will not be connected to results of self reporting at personal level.

The study has been approved by the Institutional Review Board of the National Public Health Institute, Helsinki, Finland (tusu460 9/2008). The study has been registered in Clinical Trials.gov Protocol Registration System, ID: NCT00821509.

### Study timeline

The study was started in June 2008 with the design and recruitment of participating companies. The contagion risk surveys were executed in January-February 2009. The interventions and data collection were started in February-March 2009. The interventions are planned to run 16 months (64 weeks) to cover the seasonal variation in the epidemics of the causative agents. The interventions will end in May 2010. The data analysis for the primary outcomes will start in June 2010 and is planned to end in December 2010. The total duration of the study will be two years and seven months. Additional analyses described will continue after that.

### Project administration

The project group takes care of data collection and monitoring, intervention monitoring and coordination of the sample collection and analysis. The steering committee of the study meets approximately every two months to oversee the implementation of study plan, to coordinate the interventions and to consider the conclusions of the project group.

## Results

### Data processing and basic definitions

The raw data on occurrence of RTI and GTI symptoms and associated days-off from work will be collected individually day by day but reported in blocks of seven days i.e. on weekly basis. For each cluster, the individual weekly reports will be summed together to get a number of total follow up weeks in a given cluster. Another summing up will be made for each calendar month in order to be able to analyze seasonal variation of infections and periods of sick leave from work. Individual weekly reports will be fused together to form a continuum of dates for each individual. These datasets will then be used to determine the numbers and lengths of episodes with RTI or GTI symptoms and those of associated sick leaves.

An ***infection episode ***was defined as a continuous period of time with respiratory and/or GT symptoms reported on successive days. However, in the case of a one-day interval without symptoms between symptomatic days, the flanking days with symptoms on both sides of the interval will be considered one single infection episode and the day without reported symptoms will be counted into the designated length of the episode. In the case of an interval of two or more symptom-free days, the flanking infection episodes will be considered distinct. A ***RTI episode ***and a ***GTI episode ***was determined in a similar way based on days with reported RT or GT symptoms, respectively. A ***sick leave episode ***associated with a RTI, GTI or an infection episode was defined as a continuum of successive days absent from work because of own RTI, GTI or either symptoms, respectively. The days with partial absence from work will be included in the sick leave periods. Days of absence from work flanking a week-end or other holiday of maximally two days will be included in a single sick leave episode provided that the symptoms continue through the intervening days. An ***absence episode ***due to infectious disease was defined as a continuous period of time absent from work due to own or child's RTI or GTI. Table 1 shows the links of these definitions to the alternatives in the weekly report.

**Table 1 T1:** Linkage of study definitions to the weekly report.

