### Drop-outs and post-onset enrollment of new participants

It was expected that some participants will give up weekly reporting of symptoms and days-off for various reasons or are, for operational purposes of the employer, translocated from their study cluster or leave the participating company. On the other hand, it was expected that before the end of the trial also new people are recruited by the employer to the study clusters. It was decided that since the follow-up week-based data will be primarily analyzed in a cluster specific way rather than targeting to individual participants, part time reports could be included in the data to be collected without problems. Likewise, individuals changing the study arms during the trial, first will provide data to the first arm, and after personal instructions relevant to the new arm, start to report to the other arm. Similarly, new recruits in the study clusters will be offered the possibility to participate in the trial and, after receiving training and instructions, will start reporting accordingly.

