### Study endpoints and outcome measures

#### Primary endpoints

a) the number of reported infection episodes in a cluster within a time frame of 100 reporting weeks

b) the number of reported sick leave episodes in a cluster within a time frame of 100 reporting weeks.

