### Secondary end points and outcome measures

a) the number of days with reported symptoms of RTI and/or GTI in a cluster within a time frame of 100 reporting weeks

b) the number of days-off due to own RTI or GTI in a cluster within a time frame of 100 reporting weeks

Evaluation of significance and presumptions will be the same as in primary outcome measures. As the implemented intervention presumably affects the probability to fall ill on the first hand and not so much on the duration of the illness, the potential differences in this comparison may be smaller than when using the primary end points

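### The episode definitions have no onset condition, so illness already under way at first report or after an unreported week inflates the rate by an amount that depends on how long and how continuously people report

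*Protocol article*

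**What the plan says.** All references are to the protocol article.

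- **Infection episode** (Data processing and basic definitions): it "was defined as a continuous period of time with respiratory and/or GT symptoms reported on successive days". A single symptom-free day is absorbed into the episode. For longer gaps, "In the case of an interval of two or more symptom-free days, the flanking infection episodes will be considered distinct".
- **Sick leave episode** (same section): it "was defined as a continuum of successive days absent from work because of own RTI, GTI or either symptoms, respectively". Weekends or holidays of up to two days are bridged if symptoms continue through them.
- **Denominator** (same section): "the individual weekly reports will be summed together to get a number of total follow up weeks in a given cluster".
- **First primary endpoint** (Primary endpoints): "the number of reported infection episodes in a cluster within a time frame of 100 reporting weeks". The second has the same form for sick leave episodes.
- **Partial follow-up** (Drop-outs and post-onset enrollment of new participants): "part time reports could be included in the data to be collected without problems". Late recruits are trained and then start reporting. People who change arm report first to the old arm and then to the new one.
- **Start** (Study timeline): "The interventions and data collection were started in February-March 2009". No run-in period is described.
- **Mechanism** (Secondary end points and outcome measures): "the implemented intervention presumably affects the probability to fall ill on the first hand".

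**The concern.** The separation rule works only between two runs that are both reported. It cannot act on a run that is already in progress on the first reported day, because nothing is recorded before that day. Table 1 classifies each day by status and has no onset item. As written, the rule therefore counts such a run as an episode, and as a sick leave episode if the person is absent.

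The numerator then holds episodes that began outside the weeks in the denominator. Each entry into reporting adds a fixed expected number of them, however long the person goes on to report. The endpoint is meant to be a rate, but it comes to depend on length and continuity of reporting.

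Two things are at stake. An illness that began before guidance cannot have been prevented by it, so it dilutes an effect the plan expects to act on falling ill. And if people in one arm report for shorter spells or with more gaps, that arm's rate is raised for reasons unrelated to infection risk.

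**Working it through.** The plan states no event rate, episode length or sample size, so there is no figure of its own to reproduce.

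**Inputs from the article:** follow-up of 64 weeks (Study timeline); a first analysis part of 25 weeks (the section on the unscheduled interim analysis); an expected effect near the lower end of 10-50% (Outcome measures). The two analysis parts add to 25 + 43 = 68 weeks rather than 64, which does not matter here.

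**Assumed:** mean episode length D = 5 to 10 days, with 8 as a central value, and a constant onset rate L per person-week.

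**Formula.** A person reporting w weeks has L × w new episodes. The expected number already in progress at first report is L × D/7. The counted rate is therefore L × [1 + D/(7w)], and the relative inflation is D/(7w).

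| w (weeks) | D = 5 | D = 8 | D = 10 |
|---|---|---|---|
| 4 | 5/28 = 17.9% | 28.6% | 35.7% |
| 25 | 5/175 = 2.9% | 4.6% | 5.7% |
| 64 | 5/448 = 1.1% | 1.8% | 2.2% |

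**Simulation check.** The article's rule was applied to simulated daily data, assuming 3 onsets per person-year, D = 7 and geometric durations. As written, it gave 6.57 episodes per 100 weeks at w = 4, 5.60 at 25 and 5.46 at 64. Counting only onsets inside the window gave 5.35, 5.41 and 5.38, with no trend in w.

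**Sick leave.** Here D is the length of leave. For an illustrative 2-day leave over 25 weeks, the inflation is 2/175 = 1.1%.

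**Unreported weeks.** Each return acts as a new entry. Take 25 weeks with five isolated missed weeks: 20 reported weeks and 6 entries. The formula gives 6 × D/(7 × 20), which is 21% at D = 5 and 34% at D = 8. Simulation gives 18% and 32%, or 14% and 20% if runs on either side of a gap are joined. The gap pattern is an assumption.

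**Mixed cluster.** Suppose 30% of people report 4 weeks and 70% report 25, with D = 8. Mean reporting is 0.3 × 4 + 0.7 × 25 = 18.7 weeks, so inflation is 8/(7 × 18.7) = 6.1%. If everyone reports 25 weeks it is 4.6%. The ratio is 1.061/1.046 = 1.015, a difference of about 1.5%.

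**Dilution with equal reporting in the arms.** Take a true 10% reduction, with entry illness at the control rate in both arms. Over 25 weeks with D = 8, the observed ratio is (0.90 + 0.046)/(1 + 0.046) = 0.904, a 9.6% reduction (9.7% at D = 5, 9.5% at D = 10). Over 64 weeks with D = 8 it is 9.8%. Illness that begins in an unreported week after guidance raises the level in both arms but, with equal gaps, leaves the ratio unchanged.

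**The case against.** **Silence rather than error.** An article condenses a fuller protocol, and nothing in it expressly says that illness in progress at entry is counted. This does not dispose of the point. The article goes into one-day gaps, weekends and partial days, and declares partial reports unproblematic. A rule set out at that level and applied as written counts these runs.

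**Timing at entry.** The timeline does not give the order of guidance and first report for an individual, and late recruits are trained before they report. This stands: illness at entry may precede the intervention, but the text does not show that it always does.

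**Small size, and turnover is monitored.** For continuous reporters the size is indeed small. The section on matching and comparability compares drop-outs and new recruits between clusters and arms, which would reveal a difference in turnover. It does not correct the count.

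**Stronger readings that the article does not support.** A reader might infer a distortion of about 7%, close to the expected effect. At D = 8 this arises if 30% of a cluster's person-weeks come from 4-week reporters and the rest from 25-week reporters: (0.3 × 1.286 + 0.7 × 1.046)/1.046 = 1.069. In people, 0.3/4 = 0.075 against 0.7/25 = 0.028, so about 73% of participants would have reported for only 4 weeks. Nothing in the article suggests that, and an arm-level bias of this size would need it throughout one arm's seven clusters and not in the other arm. A reader might also infer that a February-March start fell at peak incidence and enlarged the entry share. The article does not say when the peak falls.

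**Conclusion.** The point holds as a definition that should be tightened. The episode rule for both primary endpoints makes the rate depend on reporting pattern, by about 3-6% over 25 weeks and 1-2% over 64 weeks of unbroken reporting. It is much more for people who report for a few weeks or with frequent gaps. These figures rest on an assumed D of 5 to 10 days and a constant onset rate; for sick leave they are lower if leave is shorter than symptoms.

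With equal reporting patterns the effect on the comparison is slight, a 10% reduction read as about 9.6% in the first part. The arm comparison is biased only if turnover or gaps differ between arms, and the article gives no evidence that they do. It follows that partial reports are not entirely free of problems for this endpoint, but not that the trial's comparison is invalid.

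**What to change.** Add an onset condition to the endpoint derivation, identical in all three arms:

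1. **Counting.** After each entry into reporting, count an infection episode only if at least two reported symptom-free days precede it, and a sick leave episode only if at least two reported leave-free days precede it. A weekend or short holiday bridged under the existing definition does not count as leave-free. Within unbroken reporting the existing separation rules stay as they are.
2. **Where it applies.** At first report, for late entrants, after any unreported week and after a change of arm. Assign an episode that spans the end of July 2009 to the analysis part in which it began.
3. **Clock.** Start reporting time by the same rule in every arm, for example on the third reported day after each entry whatever the symptoms on the first two. Do not start it at guidance in the intervention arms and at first report in control, because that could itself create an imbalance in calendar time. In a simulation of this clock (3 onsets per person-year, D = 8), the rate was 5.35, 5.33 and 5.34 per 100 weeks at 4, 25 and 64 weeks.
4. **Sensitivity analysis.** Report the all-episode count alongside.

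The daily data already collected suffice. The cost is some extra programming and a small loss of episodes and of the first days of follow-up after each entry.

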	**"Symptoms" mean symptoms of respiratory infection or vomiting/diarrhea disease**							
	**Healthy at work or out of work as designed**	**At work with symptoms**	**Symptoms, but not supposed to be at work**	**Part of the day at work with symptoms**	**Absent due to symptoms**	**Absent due to child's symptoms; own symptoms as well**	**Absent due to child's symptoms; self healthy**	**Other reason for absence**
	
Infection episode*		x	x	x	x	x		
Sick leave episode				x	x			
Absence episode				x	x	x	x	

* RTI and/or GTI episodes will be defined the same way based on reported RTI and/or GTI symptoms

### Evaluation of matching and comparability between the arms

As the participants in the study clusters evidently will partially change during the course of the trial, because of drop-outs and new recruitments, the matching of the clusters within each triplet and the comparability between the intervention arms will be confirmed

a) by repeating at the end of the trial the questionnaire-based interview inquiring individual transmission risks (the questionnaire that was used for matching).

b) by assessing the number of participating persons in each cluster at six month intervals: the variation (the number of drop-outs and new recruits) will be compared between the clusters in each triplet and between the intervention arms.

c) by assessing similarity of results in the evaluation of the intervention implementation between the clusters in each triplet and between the intervention arms (survey for hand hygiene behavior).

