### Cluster matching and randomization

To minimize the effect of confounding factors the intervention clusters were matched and randomized prior to onset of the interventions. A questionnaire enquiring, among other things, about numbers and ages of children, their possible out-of-home day care, personal properties such as smoking, chronic diseases, and potential differences in contacts to other people during the daily work, was sent by email to all employees of the selected clusters (Additional file 1). An arbitrary virus transmission risk score was calculated for each cluster based on the results of these potential participant questionnaires [12]. First, the occurrence of each risk factor in a given cluster in relation to the frequency of the factor in the entire population interviewed was assessed. Next, these ratios were inter-connected to reveal an arbitrary transmission risk sum score for the cluster using the following formula:

Indicator variables:

x1 school aged or younger children

x2 at least one child under school age attending day care/pre-school classes/weekly club

x3 smoking (0 = if 1 or 2, otherwise > 1, see questionnaire in Appendix 1)

x4 medically diagnosed chronic heart condition, atherosclerosis, asthma or other respiratory disease

x5 mainly use of public transportation for commuting to work

x6 grown-up exposed to children with cold or vomiting/diarrhea disease at work in school, kindergarten, children's club, health care etc.

where s1-s6 denote corresponding unit-wise sums of each indicator, m1-m6 corresponding total sums over all clusters, i.e. border sums describing frequency of a given variable in the complete material and n, number of people in the cluster.

As can be judged from the above, living with pre-school children in day-care was considered the relatively strongest risk factor and the corresponding risk ratio multiplied by two in the formula. The clusters were then divided in groups of three most similar based on the calculated scores, and members of each triplet were randomized in one of the two intervention arms or in the control arm.

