### Intervention arms and arm-specific guidance of hand hygiene and behavioral habits

A total of seven office units (247 reporting persons) belonged to intervention arm 1 (IR1), in which the intervention was based on hand-washing with soap and water. Further seven office units (199 reporting persons) belonged to intervention arm 2 (IR2), the alcohol disinfectant group. The remaining seven units (218 reporting persons) served as a control arm (IR0). The interventions were planned to continue more than 12 months, preferably one and a half year, in order to cover various season-dependent viral epidemics.

Improved hand hygiene was executed with guided hand-washing with soap and water in one intervention arm and with alcohol based hand rubbing disinfectant in the other. Participants in both arms also received identical guidance on and demonstration of how to avoid infections and how to implement contagion stopping habits. The guidance included instructions for proper coughing and sneezing, for avoiding hand shaking when possible, and frequent hand washing in office and at home. The guidance was given personally to all participants by a specifically trained research nurse and each participant also received written instructions for further reference. The participants in the intervention arms received free of charge containers of the relevant soap or disinfectant, respectively, to be used at home. Participants in the intervention arm 2 also received free of charge containers of disinfectant for personal use in the office. Participants in the control arm were advised to act as before regarding hand hygiene. Toilets and other hand washing spots in all participating clusters were equipped with the same soap, Erisan Nonsid Farmos, Finland, for hand washing. The alcohol containing hand rubbing disinfectant used was LV Käsihuuhde Berner, Finland.

The study was started in two steps following the progression of recruitment. The first batch included 12 units including 374 volunteers in total. The units were matched and randomized together to form four triplets. The second step included 9 units with 306 volunteers in total. These were matched and randomized together to form three triplets. The mean participation percentage in work units was 32.4%, which is reasonable given the large intra-class correlation [13] in the cluster expected in the study.

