### A need for unscheduled interim analysis, influenza A/H1N1 pandemic

Initially we planned that interim analyses will not be done. However, in the late summer 2009 the national preparation campaign to the expected 2009 H1N1-influenza pandemic caused increased use of hand washing and use of alcohol based disinfectant in the community including the control arm of this trial. When on one hand prompting volunteers in our intervention arms to maintain hygienic behaviors, the national campaign was likely to dilute the possible difference between control and intervention arms with the participants in the control clusters also increasingly adopting hand hygiene behavior. Awareness of the citizens and hand hygiene campaigns of the companies and occupational health clinics have placed control groups of this study in a different position in the autumn 2009 as compared to that in the beginning of the study from January 2009 on. In this unexpected and unavoidable situation we have decided to analyze the results in two parts.

a) The first part will cover reporting from the beginning of the study to the end of July 2009, 25 weeks.

b) The second part will include the reporting from the beginning of August 2009 to the end of the study (if nothing else remarkable appears), 43 weeks.

This will undoubtedly debase potential results as the follow-up weeks are decreased, but on the other hand, reports of the remaining follow-up weeks can be analyzed in a new set up. In the second part we will compare the effect of personal advice and demonstration-facilitated information to that of national campaign fortified by general employer instructions.

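### After allocation, similar hand-hygiene survey results within a triplet point to lost contrast between arms, yet the protocol counts them as confirming the matching

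*Protocol article*

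**What the plan says.** The protocol article's section *Evaluation of matching and comparability between the arms* starts from the fact that cluster membership will change through drop-out and new recruitment. It states that "the matching of the clusters within each triplet and the comparability between the intervention arms will be confirmed" in three ways: (a) repeating the transmission-risk questionnaire at the end, (b) comparing participant numbers every six months, and (c) "by assessing similarity of results in the evaluation of the intervention implementation between the clusters in each triplet and between the intervention arms". Item c names the hand-hygiene behaviour survey as its source.

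*Evaluation of adherence to instructions* describes that survey. It became the formal adherence instrument once monitoring of soap and disinfectant use proved unworkable. It was run in January-February 2009, before the arms were designated, and is to be repeated at the end of the study at the latest. The section adds: "The results of the surveys will also be used to evaluate comparability of clusters within the triplets and of the intervention arms".

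The composition of a triplet is given in *Cluster matching and randomization*: "members of each triplet were randomized in one of the two intervention arms or in the control arm". The section on the intervention arms gives the counts and the intended behaviour. Of the first batch of 12 units it says "The units were matched and randomized together to form four triplets", and of the second batch of 9, "These were matched and randomized together to form three triplets". For the controls, "Participants in the control arm were advised to act as before regarding hand hygiene".

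**The concern.** Item c uses a variable that the intervention is designed to change as evidence that clusters were well matched. One cluster in each triplet was told to carry on as usual and the other two were trained to change. On a survey taken after that training, good adherence would look like failed matching, and loss of the contrast would look like successful matching.

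What is at stake is interpretation. Beyond occasional observation by the research nurse, this survey is the only systematic evidence on whether the arms behaved differently. The authors also expect some convergence. Of the 2009 pandemic they write that "the national campaign was likely to dilute the possible difference between control and intervention arms". If the primary comparison turns out null, the reader needs this survey to show whether behaviour differed between the arms. Under item c, the same similarity that explains a null result could be cited as support for the comparison.

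**Working it through.** The protocol gives no figure for this point, so the check is structural.

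**Step 1: who is in a triplet.** The two batches give 12/3 = 4 and 9/3 = 3 triplets, 7 in all. Seven units in each of three arms make 7 × 3 = 21 clusters, which fits one soap (IR1), one alcohol-rub (IR2) and one control (IR0) cluster per triplet.

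**Step 2: what a within-triplet comparison compares.** Three clusters give 3 pairs: IR1-IR0, IR2-IR0 and IR1-IR2. Over 7 triplets that is 21 pairs.
- 2 × 7 = 14 pairs set an intervention cluster against a control.
- 1 × 7 = 7 pairs set soap against alcohol rub.
- No pair compares two clusters of the same arm.

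Every within-triplet comparison is therefore a comparison across arms.

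**Step 3: what similarity means, by survey round.** For an intervention-control pair, let *d* be the difference in hand-hygiene behaviour before allocation, *i* the later change in the intervention cluster and *c* the later change in the control cluster.
- Pre-allocation survey: observed difference = *d*. Similarity here is direct evidence of comparability.
- Later survey: observed difference = *d* + (*i* − *c*).

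For a well-matched pair (*d* = 0), the later difference is *i* − *c*:

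| Situation | *i* − *c* | Reading under item c | What it indicates |
|---|---|---|---|
| Intervention cluster adheres, control unchanged | above 0 | matching not confirmed | implementation as intended |
| Intervention cluster does not adhere, control unchanged | 0 | matching confirmed | no contrast: poor adherence |
| Both improve equally | 0 | matching confirmed | no contrast: control uptake |

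A badly matched pair can also look similar later, if *d* = −(*i* − *c*). The later difference alone therefore neither establishes nor rules out good matching. Subtracting the pre-allocation difference leaves *i* − *c*, which is the contrast.

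**Step 4: can item c be confined to the pre-allocation round?** The text does not fit that reading. Item c concerns how the intervention was implemented, and nothing had been implemented before allocation. The section is justified by membership changing as the trial runs. The adherence section refers to the surveys in the plural, right after mentioning the repeat.

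**The case against.** The strongest reply is that item c is only a descriptive check. It has no threshold and no consequence, and no cluster, triplet or endpoint analysis depends on it. *Outcome measures* compares each intervention arm with control whatever the survey shows. This stands, and it limits the size of the point.

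Two further replies are right in part. The first survey round preceded designation of the arms, so similarity in that round is a valid check. And if the phrase about intervention arms means IR1 against IR2 only, similar overall adherence there is worth checking, since the protocol presumes the two arms will do about equally well. Neither rescues the within-triplet clause, which always includes the control cluster.

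It might also be said that survey tabulation belongs in a fuller plan that is not shown. The point here is a criterion that the article does state, not a missing detail.

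Several stronger readings are tempting, and the documents do not support them:
- **Similarity would show that the intervention failed.** It would show lost contrast, which could arise with full adherence if controls also improved.
- **The protocol expects complete contamination and would pass it off as good matching.** It expects dilution. It says openly that control behaviour was influenced, splits the analysis at the end of July 2009, and recasts the second part as personal advice against the national campaign.
- **The survey is the only adherence information.** Monthly nurse visits also supply some, though only sporadically.
- **Item a is equally unsound.** Participants may join and leave, so baseline data cannot describe later joiners. The risk-score factors, such as children, smoking, chronic disease and commuting, are mostly not ones that hand-hygiene advice would alter. Repeating them is a reasonable check on composition, and item b tracks drop-outs and recruits.

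**Conclusion.** The point holds for the within-triplet part of item c, and for the matching statement in the adherence section, whenever a post-allocation survey round is used. There, similarity between intervention and control clusters indicates lost behavioural contrast, and dissimilarity is what a working intervention should produce.

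The fault touches all 7 triplets and 14 of the 21 within-triplet pairs. The other 7 pairs set soap against rub, where similar overall adherence is a fair expectation but similar method is not. The consequence is confined to how the comparability check and a null result are interpreted. A reader might infer that the sign of the trial's conclusion is at risk. It is not, because no effect estimate or test uses item c.

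The conclusion rests on two assumptions: that item c covers the end-of-study round, as its wording indicates, and that the survey can register the behaviour the intervention targets.

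**What to change.** 1. Judge hand-hygiene comparability, within triplets and between arms, on the January-February 2009 survey only.
2. Rename the end-of-study survey a measure of adherence and contrast. Report, for each triplet, the intervention-minus-control change from baseline for IR1 and for IR2 (14 differences), and state that a difference is expected. Show the control clusters' own change as well, so that poor adherence can be told apart from control uptake.
3. Look for similar implementation only among clusters of the same arm or, for overall adherence, between IR1 and IR2.
4. Keep items a and b as checks on changing composition. They also help in reading step 2, because cluster-level change mixes altered behaviour with altered membership.
5. Reword the sentence in *Evaluation of adherence to instructions* to match.

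The cost is rewording and a little extra tabulation of surveys already planned, with no new data. One limit remains: an end-of-study round falls in the second analysis period, so unless an intermediate round is held it describes the contrast in that period and not in the months to July 2009.
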